#### 4.4 Sample size calculation

##### Estimated sample size

Sample size was calculated using R (version 4.3.1), based on data from a comparable study with similar methodology and endpoint definitions (14). That reference study demonstrated a mean difference of 1.37 L in positive fluid balance at 72 hours between groups, with the intervention group showing  $0.65 \pm 2.85$  L compared to  $2.02 \pm 3.44$  L in the control group (14). The effect size (Cohen's  $d = 0.45$ ) was calculated from the reported means and standard deviations.

We conducted an a priori power analysis via a Monte Carlo simulation (50,000 replicates) assuming normal distributions for each arm with observed means and standard deviations. To accommodate unequal variances, a two-tailed Welch's t-test ( $\alpha = 0.05$ ) was applied in the simulated dataset. The simulation showed that 170 participants (85 per group) are needed to achieve 80% power to detect a statistically significant difference in the primary endpoint (IV fluid volume administered within the first three hours after study enrollment). Anticipating 10% drop-out due to loss to follow-up, study withdrawal, or protocol deviations, the total planned sample size is 188 participants (94 per group).

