  - Fluid responsive (on last measurement): patients will receive (another) 500 mL of IV fluids if considered fluid responsive (and a new Starling SV measurement will be obtained). Reassess after intervention.
  - Not fluid responsive (on last measurement): repeat measurement in 30 minutes.
    - If (MAP  $\geq 65$  mmHg and systolic blood pressure  $\geq 90$  mmHg) combined with SI  $> 0.9$ : optional 500 mL of IV fluids based on rescue rules. Reassess after intervention;
    - If MAP  $< 65$  mmHg or systolic blood pressure  $< 90$  mmHg: see above;
    - If (MAP  $\geq 65$  mmHg and systolic blood pressure  $\geq 90$  mmHg) combined with SI  $\leq 0.9$ : see below.
- MAP  $\geq 65$  mmHg and systolic blood pressure  $\geq 90$  mmHg, combined with SI  $\leq 0.9$ : no action needed.

Rescue fluids (500 mL of IV fluids) recommended if, at any time during the first 3 hours, patients have any of the following conditions:

- Severe hypotension (systolic blood pressure  $< 70$  mmHg or MAP  $< 50$  mmHg)

- Refractory hypotension (systolic blood pressure < 90 mmHg or MAP < 65 mmHg) with administration of noradrenaline at dose of 20 mcg/min or of an equivalent dose of another vasopressor)
- Lactate level > 4 mmol/liter and increasing after 2 h of therapy
- Sinus heart rate > 130 beats/min for > 15 min
- PoCUS evidence of extreme hypovolemia

All fluids administered will be balanced fluids. In addition to the fluid resuscitation as described above, all patients will receive a standard 1.5 L per day of IV fluids from the moment of ED arrival. The total volume of IV fluids will be limited to a maximum of 60 ml/kg over three hours to prevent hypervolemia.

\* Vasopressor therapy initiated according to personalized protocol will be performed in the stepwise approach of standard care. Every 30 minutes vital parameters will be repeated. According to the protocol it can be that vasopressor therapy needs to be increased or that fluids will be administered, as vasopressors can cause fluid responsiveness due to increased venous return.

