## **6.3 Summary of findings from clinical studies**

The clinical studies conducted on the Starling SV monitor have yielded a substantial amount of evidence supporting its effectiveness and safety in various clinical settings. The device offers a dynamic assessment of fluid responsiveness and has been validated through multiple clinical settings. For instance, the phase shift changes observed in the Starling SV monitor have been correlated with thermodilution cardiac output in a sample of 65,000 patients. (17,18) Additionally, independent validation studies have demonstrated its reliability compared to pulmonary artery catheter. (17)

One notable advantage of the Starling SV monitor is its accuracy, which remains unaffected by vasopressors or shock states (Waldron et al., 2014). Furthermore, it has proven to be effective not only in mechanically ventilated patients but also in spontaneously breathing patients at the emergency department (ED). (8,18,19)

In a retrospective study involving nearly 200 patients, the implementation of SV-guided resuscitation was associated with improved patient outcomes. This included a reduced length of stay in the intensive care unit (ICU), lower risk of mechanical ventilation, and decreased initiation of renal replacement therapy (RRT). (20) The study also estimated that implementing SV-guided resuscitation could lead to significant cost savings, amounting to \$14.5K per treated patient (20).

The FRESH study focused on sepsis patients admitted to the ICU and aimed to guide hemodynamic resuscitation using dynamic assessments of fluid responsiveness with the Starling SV monitor. The primary clinical outcome assessed was positive fluid balance at 72 hours or ICU discharge. The results indicated that physiologically informed fluid and vasopressor resuscitation, guided by the Starling SV monitor, was safe and associated with lower net fluid balance. This approach also resulted in reductions in the risks of renal and respiratory failure, suggesting that dynamic assessments for fluid administration could improve outcomes for septic shock patients compared to standard care. (14)

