## 8. METHODS

### 8.1 Study parameters/endpoints

#### 8.1.1 Main study parameter/endpoint

The primary end point is the volume (in liters) of IV fluid resuscitation within three hours since ED admission (excluding fluids that are administered pre-hospital)

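### The 80% power in section 4.4 was computed for 72-hour net fluid balance in ICU patients and is not established for the primary endpoint, IV volume over three hours

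*Protocol*

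**What the plan says.** Section 4.4 bases the calculation on one ICU trial, which it describes as comparable in method and in how its endpoints are defined. The effect taken from it is this: "That reference study demonstrated a mean difference of 1.37 L in positive fluid balance at 72 hours between groups". The arm values are 0.65 ± 2.85 L (intervention) and 2.02 ± 3.44 L (control). Normal data with these means and SDs were simulated, and "a two-tailed Welch's t-test ( $\alpha = 0.05$ ) was applied in the simulated dataset". The conclusion is that "170 participants (85 per group) are needed to achieve 80% power", and the protocol attaches this to its own outcome: the participants "are needed to achieve 80% power to detect a statistically significant difference in the primary endpoint". An allowance of 10% for drop-out brings the total to 188.

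Other sections define the quantities involved:
- Section 8.1.1: the primary endpoint is the "volume (in liters) of IV fluid resuscitation within three hours since ED admission", with pre-hospital fluid left out.
- Section 8.1.2: fluid balance over three hours is a separate, secondary endpoint, defined as intake minus output.
- Section 6.3, on the reference trial: "The primary clinical outcome assessed was positive fluid balance at 72 hours or ICU discharge". Its patients were in intensive care.
- Section 5.1, for both arms: "The total volume of IV fluids will be limited to a maximum of 60 ml/kg over three hours to prevent hypervolemia".

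**The concern.** A power statement belongs to the variable that was simulated. Here that variable is intake minus output accumulated over 72 hours in intensive care. The variable to be tested is intake alone over three hours in the emergency department. It cannot be negative, it starts with a bolus in both arms (section 3), and it has a protocol ceiling. Nothing in the protocol links the mean difference or the spread of the first to those of the second. No three-hour mean, SD or target difference appears anywhere.

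At stake is the only justification of the sample size for the primary endpoint. As written, ethics reviewers and readers are told that the trial has 80% power for its primary comparison. In fact N = 188 is not tied to any number of litres that the trial aims to detect.

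**Working it through.** **1. Reproducing the stated figure.** Inputs from section 4.4: means 0.65 and 2.02 L, SDs 2.85 and 3.44 L, 85 per arm, two-sided α = 0.05, Welch test.
- Standard error = √[(2.85² + 3.44²)/85] = √(19.956/85) = 0.4845 L.
- Noncentrality = 1.37/0.4845 = 2.83.
- Power = 80.3% (noncentral t). A 50,000-replicate simulation gives 80.0%.
- Drop-out: 85 × 1.10 = 93.5, rounded to 94 per arm, 188 in total.

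The calculation is sound for 72-hour balance.

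**2. Simulated variable against primary endpoint.**

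| | Simulated (4.4, 6.3) | Primary endpoint (8.1.1, 5.1) |
|---|---|---|
| Quantity | intake minus output | IV intake only |
| Window | 72 hours or ICU discharge | three hours |
| Setting | ICU | emergency department |
| Range | can be negative, no stated ceiling | not negative, at most 60 ml/kg |

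Section 8.1.2 itself lists balance and volume as different endpoints.

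**3. Do the SDs fit under the cap?** A variable confined to the range 0 to C has SD ≤ C/2 whatever its mean. C = 0.06 L/kg × weight. The protocol gives no body weights, so weight is an assumption.

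| Assumed common weight | Cap C | Largest SD at any mean |
|---|---|---|
| 60 kg | 3.6 L | 1.8 L |
| 70 kg | 4.2 L | 2.1 L |
| 80 kg | 4.8 L | 2.4 L |
| 90 kg | 5.4 L | 2.7 L |
| 100 kg | 6.0 L | 3.0 L |

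The weight needed for each SD is 2 × 2.85/0.06 = 95 kg (intervention) and 2 × 3.44/0.06 = 115 kg (control). With a floor of 0.5 L for the first bolus, the 80 kg limit drops to (4.8 − 0.5)/2 = 2.15 L.

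Varying weights loosen the bound. With an assumed mean of 80 kg and SD of 18 kg, giving the heaviest patients the full cap and all others nothing yields at most 2.89 L. That is just above 2.85 L and below 3.44 L. A protocol-compliant arm cannot show this pattern, because every patient starts with a bolus.

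**4. What 85 per arm does deliver.** The standardised difference detectable with 80% power is 0.432, so the detectable difference in litres is 0.432 × SD. All SDs and differences below are assumptions.

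| SD of three-hour volume | Detectable at 80% power | Power for 0.5 L | Power for 0.25 L |
|---|---|---|---|
| 0.75 L | 0.32 L | 99% | 58% |
| 1.0 L | 0.43 L | 90% | 37% |
| 1.25 L | 0.54 L | 74% | 25% |
| 1.5 L | 0.65 L | 58% | 19% |

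The 0.5 L column is shown because it equals one bolus in section 5.1, not because the protocol names it as a target.

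**The case against.** The strongest reply is that N may be perfectly adequate. Three-hour volumes will vary far less than 72-hour balances, and if the difference shrinks in proportion, the standardised effect carries over and so does the power. This stands as a possibility: at 85 per arm even 1.37 L would be detected with over 99% power at any SD up to 2.0 L. But the protocol does not argue this. It simulates raw litres and rests on a claimed similarity of endpoints that its own sections contradict.

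Four stronger readings are tempting, and the documents do not support them.
- **That the trial is underpowered.** A smaller SD raises power and a smaller difference lowers it. Without three-hour data the net effect is unknown.
- **That a 1.37 L difference cannot occur, or barely can, in three hours.** At 80 kg the cap is 4.8 L, so arm means 1.37 L apart fit under it. Control treatment is at the physician's discretion (section 5.1), so no control mean can be deduced. The difference is unsupported, not impossible.
- **That Cohen's d = 0.45 is an arithmetic error.** Equal weighting gives 1.37/√[(2.85² + 3.44²)/2] = 0.434. The reference trial's arm sizes are not given, however, and an assumed 2:1 split gives 1.37/√[(2 × 2.85² + 3.44²)/3] = 0.448. N came from the raw means and SDs, so it does not depend on d.
- **That a null result could not be interpreted.** The confidence interval for the difference would still interpret it.

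It is also true that the simulated normals put 41% of intervention and 28% of control values below zero. This shows that the variable is not a volume. It does not by itself change the power, because a Welch test is unaffected by shifting both arms equally. The bound in step 3 therefore does not use the means.

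**Conclusion.** The power statement is wrong as written. The 80% belongs to 72-hour net balance, and the claimed similarity of endpoints is contradicted by sections 6.3, 8.1.1 and 8.1.2. This conclusion needs no outside figure.

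The misfit of the SDs supports it but rests on body weight. At a common weight of 80 kg the limit is 2.4 L against 2.85 and 3.44 L used, and the SDs used need at least 95 and 115 kg. A very heavy population would weaken this second argument, but not the first.

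The true power could lie well above or well below 80%. For an assumed 0.5 L difference it runs from 99% to 58% over SDs of 0.75 to 1.5 L. The finding is that the stated power is not established, not that the sample is too small.

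**What to change.** Keep N = 188 and rewrite section 4.4:
1. Withdraw the statement that the 72-hour figures give 80% power for the primary endpoint, and the description of the reference trial's endpoints as similar.
2. State that 85 evaluable patients per arm give 80% power (two-sided 0.05) for a standardised difference of about 0.43 in three-hour IV volume.
3. Name a target difference in three-hour litres and say why it matters.
4. Take the SD from the department's own three-hour records and tabulate power over a range of SDs, as in step 4 above.
5. Use the endpoint exactly as in section 8.1.1. Section 4.4 counts the three hours from enrolment, section 8.1.1 from admission.

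The cost is a short extract of local records and a reworded section, with no change to the planned number of patients. The downside is that the stated power becomes conditional on an SD and may turn out less favourable than 80%. For example, 0.5 L at an SD of 1.5 L would need 142 per arm for 80% power, against 63 at an SD of 1.0 L (normal approximation). If the records point that way, the protocol should state the lower power openly.

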## 5. TREATMENT OF SUBJECTS

### 5.1 Investigational product/treatment

#### Intervention:

The investigational product in this study is the Starling SV monitor, which is a medical device manufactured by Baxter Healthcare. The Starling SV monitor is a non-invasive hemodynamic monitor that provides real-time continuous information about stroke volume index, cardiac index, cardiac output, and total peripheral resistance. In this intervention study, the Starling SV monitor is designed to assist in guiding hemodynamic resuscitation for patients with sepsis.

In the experimental group, patients will receive hemodynamic resuscitation guided by the Starling SV monitor. A dynamic assessment of fluid responsiveness using the monitor will be performed at every clinical decision point during the first three hours of study enrolment.

Vital parameters, including blood pressure and heart rate, are measured upon ED arrival (triage), immediately after administration of a fluid bolus and at least twice per hour during the first 3 hours. Lactate will be measured at ED arrival (triage) and will be repeated every two hours as long as lactate is  $> 4$  mmol/L. Fluid responsiveness will be measured by the Starling SV monitor immediately before and after the administration of fluids. Fluid responsiveness is defined as an increase in stroke volume index by at least 10% after a fluid bolus of 500 mL in 10 min.

First, we will perform the first measurement during the first administration of 500 mL of IV fluids. During both the fluid bolus, we will measure the change in stroke volume index ( $\Delta$ SVI) using the Starling SV and use the stroke volume index change in response to the fluid bolus to determine fluid responsiveness.

If, at any time during the first 3 hours, patients have: (see figure 1)

- MAP  $< 65$  mmHg or systolic blood pressure  $< 90$  mmHg:
  - Fluid responsive (on last measurement): patients will receive (another) 500 mL of IV fluids if considered fluid responsive (and a new Starling SV measurement will be obtained). Reassess after intervention.
  - Not fluid responsive (on last measurement): patients will receive vasopressor (noradrenaline), according to the standard care protocol.\*
- MAP  $\geq 65$  mmHg or systolic blood pressure  $\geq 90$  mmHg combined with SI  $> 0.9$ :
  - Fluid responsive (on last measurement): patients will receive (another) 500 mL of IV fluids if considered fluid responsive (and a new Starling SV measurement will be obtained). Reassess after intervention.
  - Not fluid responsive (on last measurement): repeat measurement in 30 minutes.
    - If (MAP  $\geq 65$  mmHg and systolic blood pressure  $\geq 90$  mmHg) combined with SI  $> 0.9$ : optional 500 mL of IV fluids based on rescue rules. Reassess after intervention;
    - If MAP  $< 65$  mmHg or systolic blood pressure  $< 90$  mmHg: see above;
    - If (MAP  $\geq 65$  mmHg and systolic blood pressure  $\geq 90$  mmHg) combined with SI  $\leq 0.9$ : see below.
- MAP  $\geq 65$  mmHg and systolic blood pressure  $\geq 90$  mmHg, combined with SI  $\leq 0.9$ : no action needed.

Rescue fluids (500 mL of IV fluids) recommended if, at any time during the first 3 hours, patients have any of the following conditions:

- Severe hypotension (systolic blood pressure  $< 70$  mmHg or MAP  $< 50$  mmHg)

- Refractory hypotension (systolic blood pressure < 90 mmHg or MAP < 65 mmHg) with administration of noradrenaline at dose of 20 mcg/min or of an equivalent dose of another vasopressor)
- Lactate level > 4 mmol/liter and increasing after 2 h of therapy
- Sinus heart rate > 130 beats/min for > 15 min
- PoCUS evidence of extreme hypovolemia

All fluids administered will be balanced fluids. In addition to the fluid resuscitation as described above, all patients will receive a standard 1.5 L per day of IV fluids from the moment of ED arrival. The total volume of IV fluids will be limited to a maximum of 60 ml/kg over three hours to prevent hypervolemia.

\* Vasopressor therapy initiated according to personalized protocol will be performed in the stepwise approach of standard care. Every 30 minutes vital parameters will be repeated. According to the protocol it can be that vasopressor therapy needs to be increased or that fluids will be administered, as vasopressors can cause fluid responsiveness due to increased venous return.

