#### 8.1.2 Secondary study parameters/endpoints

##### **Efficacy**

|                           |                                                                                                                                                                                                                                                                                                                                                                                               |
|---------------------------|-----------------------------------------------------------------------------------------------------------------------------------------------------------------------------------------------------------------------------------------------------------------------------------------------------------------------------------------------------------------------------------------------|
| Hospital admission        | 
 
Length-of-stay in hospital
 
ICU admission within 7 days (excluding subjects receiving protocolized vasopressor therapy)
 
                                                                                                                                                                                                             |
| New onset organ failure   | Any of the following within 48 hours: 
 
Rise in SOFA score of at least 2
 
Organ support (i.e. vasopressor use [non-]invasive mechanical ventilation, acute dialysis, ECMO)
 
                                                                                                                                                            |
| Fluid resuscitation       | 
 
Volume of IV fluid resuscitation within three hours (including prehospital fluids administered)
 
Volume of IV fluid resuscitation within 7 days
 
Fluid balance within three hours (i.e difference between volume of intravenous plus oral fluids and the volume of fluid output (i.e. urine output and other fluid losses))
 
 |

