## 9. STATISTICAL ANALYSIS

All collected data will be stored in the REDcap, and a complete dataset will be uploaded into R version 1.4.1106 using RStudio (2015, RStudio Team, Boston, MA, United States) for further descriptive and statistical analysis. The main analysis will be conducted based on the intention-to-treat (ITT) principle. Descriptive statistics, such as mean, median, standard deviation, and confidence intervals, will be reported for continuous variables. Categorical variables will be summarized using frequencies and percentages.

The ITT analysis will include all subjects who have signed the deferred consent (DC), met the study eligibility criteria, and were randomized to either the treatment or control arm of the study. The ITT population will be the primary and secondary analysis population for this study.

Depending on the changes in treatment arms and protocol violations, we will conduct both a per protocol (PP) sensitivity analysis and a modified intention-to-treat (mITT) analysis. These analyses will be performed to assess the robustness of the study's findings and account for variations in treatment adherence and protocol deviations.

The per protocol analysis will include only the subjects who strictly adherent to the study protocol, completed the assigned treatment as planned, and did not have any major protocol violations. The mITT analysis will include subjects who met the eligibility criteria, were randomized, and received at least one part of the allocated treatment, such as one fluid bolus based on a fluid responsiveness measurement. Unlike in the ITT analysis, participants who were randomized but did not receive any treatment will be excluded from the mITT analysis.

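### Section 5.1 sends a non-responder with one low pressure and a shock index above 0.9 both to noradrenaline and to a 30-minute wait, because one branch heading says *or* where *and* is needed

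*Protocol*

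**What the plan says.** Protocol section 5.1 (Intervention) sets the treatment rule for the experimental arm as three branches under a single lead-in that applies throughout the first three hours. No order of precedence is given.

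- **Branch 1, low pressure.** The trigger is MAP below 65 "mmHg or systolic blood pressure $< 90$ mmHg". A fluid responder gets another 500 mL. For the rest: "Not fluid responsive (on last measurement): patients will receive vasopressor (noradrenaline), according to the standard care protocol".
- **Branch 2, preserved pressure with raised shock index.** The heading reads MAP at least 65 "mmHg or systolic blood pressure $\geq 90$ mmHg combined with SI" above 0.9. A fluid responder again gets 500 mL. For the rest: "Not fluid responsive (on last measurement): repeat measurement in 30 minutes". The bullets nested below say what to do after the wait. For preserved pressure they require MAP at least 65 "mmHg and systolic blood pressure $\geq 90$ mmHg) combined with SI" above or not above 0.9. A patient with either pressure low at that point is sent back to branch 1.
- **Branch 3, no action.** MAP at least 65 and SBP at least 90, with SI at most 0.9. This also uses *and*.

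Two other places depend on which branch was followed. Section 9 says: "The per protocol analysis will include only the subjects who strictly adherent to the study protocol". Section 8.1.2 lists the secondary endpoint "ICU admission within 7 days (excluding subjects receiving protocolized vasopressor therapy").

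**The concern.** The complement of *MAP below 65 or SBP below 90* is *MAP at least 65 and SBP at least 90*. The nested bullets and branch 3 have this right. The branch 2 heading does not, so it takes in patients who already belong to branch 1.

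The choice between fluid and vasopressor according to responsiveness is the experimental intervention itself. For a hypotensive non-responder the two branches name different next steps: start noradrenaline, or wait and measure again. Three things are at stake:

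- **Care.** Noradrenaline may start about 30 minutes later than branch 1 intends.
- **Adherence.** A patient who waited followed one written instruction and not the other, so membership of the per-protocol set is open to argument.
- **Who is counted.** The ICU-admission endpoint leaves out patients on protocolized vasopressors. If the pressure recovers before the re-measurement, a patient treated at once is excluded and one who waited is not. If the pressure stays low, both reach noradrenaline and both are excluded.

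The vasopressor endpoints in section 8.1.2 (use within three hours, time to start) remain defined, but their values can depend on which branch staff follow.

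**Working it through.** The protocol states no figure to reproduce here; the check is one of logic.

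**Inputs (all from section 5.1)**

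- B1: MAP <65 or SBP <90.
- B2 as headed: (MAP ≥65 or SBP ≥90) and SI >0.9.
- B2 with *and*: MAP ≥65 and SBP ≥90 and SI >0.9.
- B3: MAP ≥65 and SBP ≥90 and SI ≤0.9.

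**Enumeration of the 8 states**

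| MAP | SBP | SI | Branches as written | Branches with *and* |
|---|---|---|---|---|
| <65 | <90 | ≤0.9 | 1 | 1 |
| <65 | <90 | >0.9 | 1 | 1 |
| <65 | ≥90 | ≤0.9 | 1 | 1 |
| <65 | ≥90 | >0.9 | **1 and 2** | 1 |
| ≥65 | <90 | ≤0.9 | 1 | 1 |
| ≥65 | <90 | >0.9 | **1 and 2** | 1 |
| ≥65 | ≥90 | ≤0.9 | 3 | 3 |
| ≥65 | ≥90 | >0.9 | 2 | 2 |

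As written, 2 of 8 states meet two branches. With *and*, every state meets exactly one. A check over 79,380 combinations of MAP, SBP and heart rate likewise found no overlaps and no gaps with *and*.

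**Alternative parsing.** The heading could be read as MAP ≥65, or (SBP ≥90 with SI >0.9). That is worse. Three states then overlap with branch 1: the two in bold, plus MAP ≥65 with SBP <90 and SI ≤0.9. Preserved pressures with SI ≤0.9 would also meet branches 2 and 3 together.

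**Patients in the overlap**, using the approximation MAP = (SBP + 2 × DBP)/3 and SI = heart rate/SBP:

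- BP 92/44, heart rate 100: MAP = (92 + 88)/3 = 60.0; SI = 100/92 = 1.09. MAP is low, SBP preserved.
- BP 88/56, heart rate 85: MAP = (88 + 112)/3 = 66.7; SI = 85/88 = 0.97. SBP is low, MAP preserved.

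**How easily the states are reached**

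- At SBP 92, MAP <65 needs DBP < (195 − 92)/2 = 51.5, and SI >0.9 needs a heart rate above 0.9 × 92 = 82.8.
- At SBP 88, MAP ≥65 needs DBP ≥ (195 − 88)/2 = 53.5, and SI >0.9 needs a heart rate above 0.9 × 88 = 79.2.

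These values are unremarkable in a population that section 4.2 selects on low MAP, low SBP, raised lactate or SI above 0.9.

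**Consequence by responsiveness**

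- Responder: both branches give 500 mL, so there is no conflict.
- Non-responder: branch 1 gives noradrenaline now. Branch 2 re-measures after 30 minutes and goes to branch 1 only if a pressure is still low. The possible delay is about 30 of 180 minutes. Neither step orders fluid.

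**The case against.** The strongest reply is that the two instructions can both be obeyed. Branch 2 does not say to withhold a vasopressor, and the footnote to the algorithm already has vital parameters repeated every 30 minutes during vasopressor therapy. A clinician who starts noradrenaline and re-measures half an hour later breaches nothing. On this view a delay arises only if branch 2 is taken to override branch 1, which the text never says, and waiting alone leaves an explicit order undone. The intended *and* can also be read off the nested bullets and branch 3. A trained research team runs the algorithm, and Figure 1, which was not available for this review, may have it right. Intention-to-treat is the primary population, with the per-protocol set a conditional sensitivity analysis. The ICU effect needs a chain of conditions, and it stems from excluding patients on a post-randomisation treatment, which the *or* did not create.

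Much of this stands. The intended meaning is recoverable, the analysis consequences are secondary, and nothing shows that the slip has reached the bedside. What does not stand is the claim that there is no conflict. Branch 2 makes the wait its action for a non-responder and reaches the vasopressor step only if pressure is low afterwards. Someone who follows it literally starts noradrenaline late while following a written instruction. The rescue rules do not close the gap: they recommend fluid, and their pressure criteria require SBP below 70, MAP below 50, or hypotension despite noradrenaline at 20 mcg/min. A correct figure would not make the text consistent.

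**Conclusion.** The concern holds: section 5.1 is wrong as written. The branch 2 heading contradicts its own nested bullets and branch 3, and gives two different next steps to a non-responder with exactly one low pressure and SI above 0.9. It is probably a wording slip, but it sits in an operative treatment rule of the experimental arm and should be corrected.

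Its reach is limited to non-responders in 2 of 8 logical states. That is a count of states, not a proportion of patients; the protocol gives no frequencies. The delay of about 30 minutes assumes that staff follow branch 2 literally and that the pressure stays low. The per-protocol and ICU-admission effects are possible rather than demonstrated. Sample size is untouched.

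**What to change.** In section 5.1, reword the branch 2 heading so that it requires MAP of at least 65 mmHg **and** SBP of at least 90 mmHg, in parentheses, combined with SI above 0.9. This matches the nested bullets and branch 3, and both discordant states then go to branch 1 alone. Check that Figure 1 and any bedside copy of the flowchart say the same.

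The cost is one word plus that check. No new data are needed, and neither the sample size nor the analysis changes.
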